### Statistical analysis

All analyses will be performed based on intention-to-treat principles, any missing data in the follow-up visits will be imputed using multiple imputation. Descriptive analyses as means and standard deviations (SDs) will be used to describe the demographics and clinical characteristics of the participants. The primary efficacy analysis compared the hair-loss grading between YH0618 granule and control before the fifth chemotherapy using Fisher’s exact test. The changes of hair diameter between the two groups after four cycles of chemotherapy will be compared by an independent samples *t* test. A multivariable logistic regression model will be used to explore the treatment effect. Potential confounding variables will be identified as those that differ among treatment groups at baseline and are significantly associated with outcomes. Changes from baseline to the final assessment in quality of life assessed by the FACT-B and objective indicators in the blood will be compared using Wilcoxon rank sum tests. Unless otherwise specified, two-sided statistical tests will be used and the significance level will be set at *p* < 0.05.

In this trial, an interim analysis will be performed when approximately two thirds of the planned observations are enrolled. The results are analyzed by the statistician and only DSMB members have access to the results to test for futility, safety and efficacy of the trial. A predefined stopping rule will be applied to the data to determine whether it is futile to continue enrollment.

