YH0618, a medicinal and edible compound prescription, is developed based on the “homology of medicine and food,” theory ancient prescription, and long clinical practice. Our previous animal studies have shown that YH0618 decoction did not interfere with the anti-tumor effects of chemotherapy drugs [12]. Additionally, a randomized clinical trial also showed that YH0618 significantly accelerated hair regrowth and reduced thumbnail pigmentation in cancer patients who have completed chemotherapy (data was not showed, but the protocol was published in [13]). Therefore, this study will further explore the efficacy of YH0618 granule on chemotherapy-induced hair loss in patients with breast cancer by a randomized, double-blind, multi-center clinical trial. YH0618 consists of five medicinal and edible foods (black soybean and liquorice, etc.) which are recommended by clinicians for cancer patients and all components have a history of safe use in other foods. Besides, each of the components possesses a distinct pharmacological profile, including removing free radicals in the body, regulating the immune system, preventing cancer, detoxifying and enhancing the sense of taste [14–16]. Black soybean and liquorice, as the main essential ingredients, have been used for detoxification for millennia in China. Based on the theory of the “Essence of the kidney is reflected on the hair” in traditional Chinese Medicine, the color, texture and growth of hair is believed to be closely related to the kidney. However, there is no in-depth research on the relationship between kidney and hair, and no research is combined with the comprehensive evaluation of renal function from the aspects of both Chinese and western medicine to explore the mechanism of chemotherapy-induced hair loss. The kidney is an important detoxification organ of the human body and helps to filter out toxins in the blood and other waste through urine. Chemotherapy drugs may not cause renal organic lesions, but they “consume” kidney essence and kidney *qi*, which breaks the balance of the body. Therefore, we believe that chemotherapy agents not only directly produce toxic effects on hair-follicle cells, but also deplete *qi*, blood and body fluids, especially kidney essence and kidney *qi*, and breaks the balance of *yin* and *yang* of the human body, which leads to the obstruction of microcirculation and the decline of immune function, further resulting in nutritional disorders of hair follicles and hair loss. Thus, the study will also elucidate the mechanism of YH0618 granule on reducing hair loss from the aspect of kidney deficiency or renal dysfunction. The hypothesis of the study is that YH0618 granules could delay chemotherapy-induced hair loss by improving kidney deficiency and renal dysfunction.

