### Estimation of sample size

The primary outcome in this study is the time point of occurrence of chemotherapy-induced hair loss reaching grade II measured by the WHO Toxicity Grading Scale for Determining the Severity of Adverse Events. Our previous results showed that YH0618 could cause the incidence of hair loss grade < II to reach 50% for patients who have completed chemotherapy, and the difference between the incidence of hair loss grade < II in YH0618 group and the control group was 15%. Thus, the difference in proportion between the two groups will be measured by a Z test. To achieve a two-sided, type-I error alpha = 0.05 and power: (1 − beta) = 80%, the minimal number of subject need in each group is 85. We estimated a 20% attrition rate at the end of follow-up; hence, a sample size of at least 107 in each group (214 in total) is planned for this study.

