### Outcome evaluation

#### Primary outcome

The primary outcome is the time point of occurrence of hair loss reaching grade II as assessed by the WHO Toxicity Grading Scale, and objective indices of hair quality and hair-follicle growth recorded by a hair and scalp detector (CBS-603, CBS, Taiwan) before the fifth chemotherapy cycle.

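### The primary hair-loss outcome is the time to grade II, but its primary test compares grade at a single visit, ignores timing, and can miss a delay that has closed by then

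*Protocol article*

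**What the plan says.** All references are to the protocol article.

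- **Outcome.** The Primary outcome section states: "The primary outcome is the time point of occurrence of hair loss reaching grade II as assessed by the WHO Toxicity Grading Scale". It adds objective hair indices from a scalp detector. Study design gives the same definition, and Estimation of sample size repeats the time component: "The primary outcome in this study is the time point of occurrence of chemotherapy-induced hair loss reaching grade II".
- **Hypothesis.** The Background ends with the expectation that "YH0618 granules could delay chemotherapy-induced hair loss by improving kidney deficiency and renal dysfunction".
- **Data.** Table 1 and the Clinical objective examination section schedule hair-loss grading at baseline, before cycles 2, 3, 4 and 5 (visits 1 to 4), and once more a month after chemotherapy.
- **Sizing.** Estimation of sample size moves from the time outcome to the share of patients below grade II and says that "the difference in proportion between the two groups will be measured by a Z test".
- **Analysis.** Statistical analysis says: "The primary efficacy analysis compared the hair-loss grading between YH0618 granule and control before the fifth chemotherapy using" Fisher's exact test. The other methods named are a t test for hair diameter, a multivariable logistic regression, and Wilcoxon rank sum tests for quality of life and blood indicators.

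**The concern.** The question asked (when does moderate hair loss occur?) is not the question tested (what is the grade just before cycle 5?). Three of the four post-baseline gradings in the treatment phase do not enter the primary test. A patient who reaches grade II before cycle 2 and one who reaches it before cycle 5 count alike, although the difference between them is the benefit that the trial hypothesises.

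This is not a detail left to a statistical analysis plan. The article commits to a specific test. A later plan that used a time-based method would contradict the Statistical analysis section, and one that followed that section would leave the time component of the outcome unanalysed. At stake is a real delay being reported as no effect, and doubt about which definition governs the conclusion.

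**Working it through.** **1. The plan's own sample size.** Inputs from Estimation of sample size: 50% below grade II with YH0618, a difference of 15 points (so 35% in control), two-sided alpha 0.05, power 80%, 85 per group, 20% attrition.

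n per group = [1.960·√(2·0.425·0.575) + 0.842·√(0.50·0.50 + 0.35·0.65)]² / 0.15² = (1.370 + 0.582)² / 0.0225 ≈ 169.3, so 170.

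The stated 85 is half of this. The attrition step is correct: 85/0.8 = 106.25, so 107. At 50% vs 35%, the Z test has 51% power with 85 per group and 60% with 107; Fisher's exact test has 45% and 54%. The factor of two is a separate matter, but it means that the stated 80% cannot be carried over to any test at this size.

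**2. A time-based test under the planning rates.** Assumptions: 50% vs 35% below grade II before cycle 5, and constant hazards.

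- Hazard ratio = ln 0.50 / ln 0.35 = 0.66.
- Events for 80% power (Schoenfeld) = 4·(1.960 + 0.842)² / (ln 0.66)² ≈ 182.2, so 183.
- Share with an event = (0.50 + 0.65)/2 = 0.575. So 183/0.575 ≈ 319 patients, or about 400 after 20% attrition.
- With 85 per arm: 170·0.575 ≈ 98 events, power about 54%. With 107 per arm: 214·0.575 ≈ 123 events, power about 63%.

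**3. Single visit against all four visits.** Simulated trials with 85 per arm and grade dichotomised at II: Fisher's exact test at visit 4 against a grouped log-rank test over visits 1 to 4. All curves are assumptions.

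| Below grade II at visits 1–4, YH0618 vs control (%) | Fisher | Grouped log-rank |
|---|---|---|
| 84/71/60/50 vs 77/59/46/35 (constant hazards, planning rates) | 45–47% | 53–54% |
| 86/72/60/50 vs 80/60/45/35 (hazard ratio 0.65) | 47–49% | 56% |
| 72/46/29/14 vs 60/30/15/5 (hazard ratio 0.65) | 46% | 74% |
| 100/77/59/46 vs 77/59/46/35 (shift of one cycle) | 24% | 60% |
| 80/50/25/15 vs 60/30/15/10 (nearly converged) | 12% | 70% |
| 80/50/20/5 vs 50/20/6/5 (converged) | 2% | 97% |
| 95/75/50/35 vs 80/60/45/35 (small early gap, closed) | 3% | 14% |

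The time-based test has higher power in every row. The margin is 7 to 9 points where the 15-point gap persists and very large where the curves separate early and then meet. The last row shows its limit: a small, short-lived delay is missed by both tests.

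**The case against.** The strongest reply is that the single-visit test is a reasonable choice on the protocol's own assumptions. It plans for a 15-point difference in the share below grade II, and if that gap exists before cycle 5, Fisher's test gives up only 7 to 9 points of power. That stands. A reader might infer that the test cannot detect a delay at all, and the documents do not support this. It is near-blind only if the arms have met by visit 4. The Background's 80–100% figure makes that plausible, but it is the incidence of any hair loss with specific agents, not of grade II or worse by cycle 5. The planning rates imply about 50% vs 65% at grade II or worse, although they come from patients who had completed chemotherapy.

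Four further points limit the finding:

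- A reader might count three rival primary analyses. The Z test and Fisher's test address the same contrast of proportions, so the conflict is two-way: time against status at one visit.
- A reader might say that the primary outcome is never analysed. Hair diameter, an objective index, is tested; only the time component is left out.
- A reader might hold that Fisher's test is incompatible with the plan that "any missing data in the follow-up visits will be imputed using multiple imputation". The same table yields a log odds ratio or risk difference with a standard error, which can be pooled, and how to do so is ordinary detail for an analysis plan.
- The Statistical analysis section does not say that grade is dichotomised. A comparison across all five grades could pick up differences in severity that the figures above do not reflect.

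Redefining the outcome as the proportion at or above grade II before cycle 5 would also restore consistency, but it would no longer test the stated delay directly. None of this removes the mismatch.

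**Conclusion.** The contradiction holds and rests on the text alone: a time outcome and a delay hypothesis are paired with a primary test of grade at one visit, and no listed method uses time. The consequence is conditional. At 85 per arm the loss is modest (about 45–49% against 53–56%) if a gap of about 15 points remains before cycle 5, and large (12% against 70%, or 2% against 97%) if the arms have nearly or fully converged. These figures assume grade dichotomised at II and illustrative event curves. The document does not show which situation applies, so the claim is that the test can miss a delay that has closed by then, not that it will.

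**What to change.** Make the primary hair-loss analysis match the outcome: time, in cycles, to first grade II or worse over visits 1 to 4, treated as grouped or interval-censored. A discrete-time complementary log-log model reporting a hazard ratio with 95% CI would serve. Keep the proportion below grade II before cycle 5 as a secondary analysis, reported as a risk difference with CI. Use the same definition in Study design, Estimation of sample size, Primary outcome and Statistical analysis.

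Restate power for the chosen test at the planned size: under the planning rates with constant hazards, about 54% with 85 per arm and 63% with 107. Settle this before unblinding and before the interim look.

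The cost is a change of wording and a less favourable power statement. No new data collection is needed, because the gradings are already scheduled. The change does not restore 80% power; under these rates that would take about 400 patients after attrition.

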## Background

Chemotherapy is a major type of cancer treatment using chemical medications to affect cancer cell growth, division and reproduction. Regardless of the route of administration, chemotherapy drugs are introduced into the blood stream, so that chemotherapy can cause various degree of damage to other normal organs and tissues while killing cancer cells, further causing a series of serious adverse effects/toxicity.

Hair loss is an obvious side effect of chemotherapy. The incidence of chemotherapy-induced hair loss is as high as 65% in patients receiving chemotherapy and in some is even up to 80–100% in patients receiving specific agents, such as doxorubicin and docetaxel [1–3]. Although hair loss itself does not cause damage to the body and threaten life, it can induce persistent negative emotions such as anxiety, depression and negative evaluation of self-image, which in turn reduces quality of life [4]. The hair loss caused by chemotherapy is usually reversible; however, in most cases, the color of the new hair is grayish or different from the previous color, and the hair texture also shows some changes, such as being rougher, slower growing and sparser [5, 6]. Besides, contemporary social media and excessive attention to appearance have put more pressure on patients, with 8% of patients saying that they refuse chemotherapy because of fear of alopecia [7]. Even some female patients said that having no hair is more difficult to tolerate than mastectomy [8].

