### Subjects

A total of 214 eligible patients will be recruited at different clinical centers. Inclusion criteria include: (1) women with stage-I or -II breast cancer aged between 18 and 75 years; (2) receiving first chemotherapy; (3) planning to receive chemotherapeutic agents containing taxanes or/and anthracyclines; (4) the chemotherapy regimen will last for at least six cycles with every 3 weeks a cycle; (5) adverse events assessed using WHO toxicity classification criteria < grade II; and (6) a life expectancy of at least 6 months. Exclusion criteria are: (1) patients with a medical history of hair transplantation; (2) patients suffering from psoriasis or severe scalp infection; (3) hair loss induced by alopecia areata, alopecia totalis or scalp injury, etc.; (4) pregnancy, lactation or potential pregnancy; (5) allergy to some specific foods, like black soybean; (6) severe cardiac, hepatic, renal, pulmonary and hematic lesions or other diseases which will affect their survival; (7) those who have any severe mental or behavioral disorders who cannot be fully informed; (8) suspected of or with a history of alcohol and/or drug abuse; (9) cannot understand or fill in questionnaires because of cognitive disorders or a low level of literacy; and (10) a variety of factors affecting drug taking and absorption, such as the inability to swallow, chronic diarrhea, intestinal obstruction, etc. Eligible patients will be invited to participate in this study after obtaining their written consent form. All participants will be closely monitored in the study.

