### Grading of chemotherapy-induced hair loss

The WHO Toxicity Grading Scale is commonly used to monitor and rate the severity of anticancer drug-induced toxicity [19, 20]. The grading criteria for hair loss is shown in Table 2. Alopecia assessments will be conducted by a clinician blinded to treatment assignment, and by the participant.

**Table 2 Tab2:** World Health Organization (WHO) grading criteria for anti-drug induced hair loss

Grade 0	No hair loss
Grade I	Minor hair loss
Grade II	Moderate hair loss/alopecia areata
Grade III	Complete hair loss with regrowth
Grade IV	Non-regrowth hair loss

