#### Objective measurement of hair loss

In order to objectively evaluate the hair quality and hair-follicle growth, a hair and scalp detector (CBS-603) will be used. The detector obtained patents in the United States, German, Japan, China, and China Taiwan, and many international authentications from Conformité Européenne (CE), Federal Communications Commission (FCC), and Restriction of Hazardous Substances (RHoS). The detector is composed of a 10X-200X Hair and Scalp Camera and software. The whole top of the head, a wide range of hair loss and the condition of hair follicles could be clearly filmed at 10X, 50X and 200X, respectively. The software has a function of testing through which hair testing and analysis can be conducted. In this study, identification and classification of the level of hair loss, hair diameter and quality will be analyzed.

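### Hair diameter is undefined for patients with no measurable hair, and the stated multiple-imputation rule, taken literally, would give them a modelled diameter

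*Protocol article*

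**What the plan says.** In the Protocol article, the Primary outcome section names the time at which hair loss reaches grade II "and objective indices of hair quality and hair-follicle growth recorded by a hair and scalp detector (CBS-603, CBS, Taiwan) before the fifth chemotherapy cycle". Under Objective measurement of hair loss, "identification and classification of the level of hair loss, hair diameter and quality will be analyzed", so diameter is one of these indices. Table 1 schedules them, under primary outcomes, at baseline and every later visit.

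The Statistical analysis section fixes two rules for diameter. The test is: "The changes of hair diameter between the two groups after four cycles of chemotherapy will be compared by an independent samples" *t* test. For incomplete data, under intention to treat, "any missing data in the follow-up visits will be imputed using multiple imputation". No exception is stated for patients without hair.

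The document also shows that absence of hair can be expected. Table 2 defines grade III as "Complete hair loss with regrowth". The Subjects section requires patients "planning to receive chemotherapeutic agents containing taxanes or/and anthracyclines". The Discussion associates severe loss with several of these drugs and lists alopecia totalis among its presentations.

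Other parts give diameter less weight. Estimation of sample size names only grade II hair loss as the primary outcome, and Statistical analysis reserves its primary efficacy comparison for the grading, by Fisher's exact test.

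**The concern.** Where there is no shaft, a diameter is not an unobserved number but an undefined one. Its absence is a form of the failure that the trial sets out to measure. Multiple imputation is built for values that exist and were not seen. Used here, it predicts a diameter from patients who kept their hair, so a patient with complete loss enters the *t* test as if she had ordinary hair. Leaving such patients out is no better: it compares groups selected by what happened after randomisation, and it departs from the stated intention-to-treat principle.

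The trial's hypothesis is that YH0618 affects hair loss, so unequal retention is the situation the trial plans for. The diameter comparison could then miss a real benefit in retention, or show a diameter difference that only reflects who still had hair. Diameter is the only detector index for which the article names a test of its own.

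**Working it through.** The protocol gives no planning figure for diameter, so there is none to reproduce. The steps below bound what can be said.

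**1. How many patients could be affected.** Estimation of sample size gives 50% at grade < II with YH0618 and a difference of 15 points. Reading control as 50% − 15% = 35%, grade II or worse is 50% and 65%. With the planned 85 evaluable patients per arm:
- YH0618: 85 × 0.50 = 42.5
- control: 85 × 0.65 = 55.25

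On these planning rates these are upper bounds for patients without measurable hair, because grade II is only moderate loss. The share with complete loss is not given.

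**2. Whether the direction is fixed, if only patients with hair are compared.** Assume retention of 75% (YH0618) and 60% (placebo), no effect on diameter, and retention decided entirely by one standard normal variable. The mean of that variable in the upper fraction *p* is φ(z)/*p*:
- *p* = 0.75: 0.424
- *p* = 0.60: 0.644
- difference: 0.424 − 0.644 = −0.22 SD

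This is the difference in the variable that drives retention. The plan tests change. With equal unit variances and baseline–follow-up correlation r = 0.5, the SD of change is √(2(1 − r)) = 1, and:
- selection on follow-up diameter: (1 − r)(−0.22) = −0.11 SD, against YH0618
- selection on baseline diameter: −(1 − r)(−0.22) = +0.11 SD, in favour of YH0618

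The sign depends on a mechanism that the document does not describe.

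**3. Bias under the stated imputation.** This was simulated with 85 per arm and 1,500 runs per setting. Treatment changes retention only. Diameter change has SD 1 and correlation ρ with the variable that decides retention. Imputation (10 sets) uses arm and a prior-visit value correlated 0.5 with the change and available for everyone. All of these inputs are assumptions.

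| Complete loss, YH0618 / placebo | ρ | Imputed difference (SD) | *t* test rejects | Worst-rank test rejects |
|---|---|---|---|---|
| 5% / 20% | 0 | −0.001 | 4.6% | 39.6% |
| 5% / 20% | 0.5 | −0.098 | 10.1% | 18.2% |
| 5% / 20% | 0.7 | −0.132 | 12.7% | 12.5% |
| 20% / 35% | 0 | −0.001 | 5.3% | 40.8% |
| 20% / 35% | 0.5 | −0.086 | 7.8% | 25.2% |
| 20% / 35% | 0.7 | −0.122 | 11.9% | 20.7% |
| 35% / 50% | 0 | 0.001 | 4.6% | 42.8% |
| 35% / 50% | 0.5 | −0.079 | 7.6% | 32.9% |
| 35% / 50% | 0.7 | −0.132 | 11.9% | 26.3% |
| 50% / 65% | 0 | −0.004 | 5.5% | 48.7% |
| 50% / 65% | 0.5 | −0.101 | 7.2% | 36.8% |
| 50% / 65% | 0.7 | −0.146 | 11.1% | 37.1% |
| 35% / 35% | 0 | 0.001 | 5.2% | 4.4% |
| 35% / 35% | 0.5 | 0.002 | 4.8% | 5.7% |
| 35% / 35% | 0.7 | −0.002 | 4.7% | 4.5% |

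The bias is zero, within simulation error, when ρ = 0 or when loss is equal. Otherwise it reaches about 0.15 SD. The minus sign follows from the assumed positive ρ; a negative ρ would reverse it. In the rows with unequal loss, the worst-rank test rejects more often than 5% because it counts a real retention benefit. At ρ = 0 the imputed *t* test is unbiased for diameter but shows none of that benefit.

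**4. Baseline adjustment.** With equal variances, the ANCOVA variance relative to that of the change score is (1 − r²)/(2(1 − r)) = (1 + r)/2. At r = 0.5 this is 0.75, a 25% reduction.

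**The case against.** The strongest reply is that the article never classes absent hair as missing data. A diameter that does not exist need not fall under a missing-data rule, and an analysis plan that is not shown could say how it is handled. A reader might infer that the trial will certainly impute diameters for bald patients; the text does not support that. What stands is narrower. The protocol itself fixes a *t* test on change and imputation of any missing follow-up value, and together these rules are unsuitable for this endpoint unless an exception is written.

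The extent is also uncertain. The Background figure, "even up to 80–100% in patients receiving specific agents, such as doxorubicin and docetaxel", is for hair loss of any degree. A reader might take it as the rate of complete loss, but no such rate is given. Grade III includes regrowth, and the detector magnifies up to 200 times, so some of these patients may still have hairs that can be measured.

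Nor is a change-score *t* test invalid in itself: it subtracts baseline and is unbiased under randomisation when every patient has a value. The case for ANCOVA is one of efficiency.

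Finally, scoring complete loss as worst moves the diameter endpoint towards a second hair-loss comparison. That is true, and it is a real cost of the remedy.

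**Conclusion.** The point holds in a limited form. The diameter endpoint is not defined for patients with no measurable hair, and the stated rules, read literally, replace that failure with a modelled value. The comparison is biased only if retention differs between arms and is related to diameter change. Under the assumed complete-loss shares (5% to 65%, 15 points apart) and correlations up to 0.7, the bias is 0 to about 0.15 SD, with rejection of up to about 13% against a nominal 5%. These figures are illustrations and cannot be derived from the document.

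Two stronger readings should be resisted. One is that the result would necessarily point against YH0618: the −0.22 SD above applies to the variable that drives retention in a comparison of patients with hair, which is not the planned analysis, and on change scores the sign can go either way. The other is that the trial's main conclusion is at risk. The objective indices do stand under the primary outcome, but the sample size and the named primary efficacy analysis rest on the grading, where complete loss already counts as failure. That analysis is untouched.

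**What to change.** 1. For the diameter comparison, rank patients with no measurable hair before the fifth cycle below all others, compare arms by a rank test, and report a win probability.
2. Limit multiple imputation to values that exist but were not observed, such as those from missed visits. The case record must then separate a visit that was missed from a detector reading that found no hair to measure.
3. Report diameter among patients with measurable hair as supportive only, by ANCOVA on baseline diameter in place of the change-score *t* test. This improves precision but does not remove the selection.

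The cost is analysis wording and one recorded distinction; grade and detector readings are already scheduled at every visit. The effect is no longer a simple difference in micrometres, and the ranked endpoint partly overlaps the hair-loss grading comparison, so the two results should not be presented as independent evidence.

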**Fig. 1 Fig1:**
[figure not shown]
Flow chart of the clinical trial

**Table 1 Tab1:** Trial process chart

	Before baseline screening	Baseline	Visit 1 treatment phase	Visit 2 treatment phase	Visit 3 treatment phase	Visit 4 treatment phase	Visit 5 follow-up phase
		(before chemo)	Before 2nd chemo	Before 3rd chemo	Before 4th chemo	Before 5th chemo	1 month after chemo
Patients							
Inclusion and exclusion criteria	×						
Informed consent		×					
Demographics		×					
Medical characteristics	×	×	×	×	×	×	×
Randomization and allocation concealment		×					
Primary outcomes							
Grading of hair loss		×	×	×	×	×	×
Objective indices (hair quality and hair follicles)		×	×	×	×	×	×
Secondary outcomes							
Facial color and thumbnail color		×	×	×	×	×	×
Grading of thumbnail ridging		×	×	×	×	×	×
Quality of life and fatigue		×	×	×	×	×	×
Routine blood test		×	×	×	×	×	×
Liver function (ALT, AST, total protein, and Alba)		×	×	×	×	×	×
Renal function (Cr, UA and BUN)		×	×	×	×	×	×
Kidney deficiency (IgM, C3、CD4 +, CD8 + Mg^2+^, Cu^2+^, Zn^2+^, Fe^3+^)		×		×		×	
Adverse events			×	×	×	×	×
Patients’ diary records			Every day during the study				

*BUN* blood urea nitrogen, *Cr* creatinine, *ALT* alanine aminotransferase, *AST* aspartate aminotransferase

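### Hair diameter, FACT-B and blood indicators are compared as unadjusted changes although their baselines are collected: the tests are valid, but usually less precise than baseline-adjusted ones

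*Protocol article*

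**What the plan says.** Under Statistical analysis, the protocol article assigns hair diameter this comparison: "The changes of hair diameter between the two groups after four cycles of chemotherapy will be compared by an independent samples" t test. For quality of life the outcome is "Changes from baseline to the final assessment in quality of life assessed by the FACT-B", and this together with "objective indicators in the blood will be compared using Wilcoxon rank sum tests". No covariate is attached to any of these tests.

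The only adjusted model in the section is logistic: "A multivariable logistic regression model will be used to explore the treatment effect". Its covariates are to be found from the data: "Potential confounding variables will be identified as those that differ among treatment groups at baseline and are significantly associated with outcomes".

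The baselines exist. Table 1 (Trial process chart) marks "Objective indices (hair quality and hair follicles)" and "Quality of life and fatigue" at baseline and at all five later visits. It also marks the blood tests at baseline. The section on clinical objective examination places an assessment within 3 days before each cycle from the first to the fifth.

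The Primary outcome section includes the objective indices from the hair and scalp detector, measured before cycle 5. The section on objective measurement of hair loss lists hair diameter among the quantities to be analysed.

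**The concern.** A change score uses the baseline in one fixed way: it subtracts it with a slope of 1. The slope that the data support is usually different. The mismatch has two consequences.

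- **Precision.** The standard error of the treatment contrast is larger than it need be, with no saving in data collected.
- **Imbalance.** If the arms happen to differ at baseline, part of that difference stays in the estimated effect. Blocks of four, as described under Randomization and blinding, balance numbers per arm and not baseline hair diameter or FACT-B score.

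The logistic model does not help, because it is meant for a binary outcome. Even there, the baseline value of the outcome is not a prespecified covariate.

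Hair diameter matters most, since it belongs to the primary outcome and is the only detector measure that the section gives a named test.

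**Working it through.** **Inputs.** The tests, the outcome form (change) and the baseline measurements are as stated above. The article gives no SD, correlation, effect size or power for hair diameter, FACT-B or the blood indicators, so there is no planning figure to reproduce on this point. The one sample-size figure, 85 per group, was derived for the proportion with hair loss below grade II. It serves here only as a convenient group size. (That figure does not follow from 50% against 35%, which needs 170 per group at two-sided 0.05 and 80% power. This is a separate matter on which nothing below depends.) The correlation r and the SD ratio k = SD at follow-up / SD at baseline are assumptions, so ranges are shown.

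**General formulas**, with the baseline SD set to 1:

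- Variance of the change: 1 + k² − 2rk
- Residual variance under ANCOVA: k²(1 − r²)
- Difference between the two: (1 − rk)²

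The difference is a square, so in large samples ANCOVA is never less precise. The two are equal only when the slope rk is exactly 1. Given a baseline imbalance D, the change-score estimate is shifted by −(1 − rk)D. The ANCOVA estimate is not shifted.

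**Equal SDs (k = 1).** The variance ratio is (1 − r²)/(2(1 − r)) = (1 + r)/2. With 85 per group:

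| r | Variance, ANCOVA / change | Standard error lower by | n per group for ANCOVA to match 85 | ANCOVA power where change-score t test has 80% | Size of shift in change-score estimate at 0.2 SD imbalance |
|---|---|---|---|---|---|
| 0.3 | 0.65 | 19.4% | 56 | 93.5% | 0.14 SD |
| 0.5 | 0.75 | 13.4% | 64 | 89.9% | 0.10 SD |
| 0.7 | 0.85 | 7.8% | 73 | 86.0% | 0.06 SD |
| 0.9 | 0.95 | 2.5% | 81 | 82.0% | 0.02 SD |

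For example, at r = 0.3: 85 × 0.65 = 55.25, so 56; and 0.2 × (1 − 0.3) = 0.14. The shift has the opposite sign to the imbalance.

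**Simulation** (normal data, equal SDs, 85 per group, 4,000 trials for each r). Power for the t test on change, the Wilcoxon test on change and ANCOVA was 0.80/0.77/0.94 at r = 0.3, 0.79/0.77/0.89 at r = 0.5 and 0.79/0.77/0.85 at r = 0.7. The slope of the change-score estimate on the baseline imbalance was −0.70, −0.51 and −0.29. For ANCOVA it lay within about 0.012 of zero.

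**Unequal SDs.**

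- k = 1.5, r = 0.6: the slope is 0.9. The change variance is 1 + 2.25 − 1.8 = 1.45 and the ANCOVA variance is 2.25 × 0.64 = 1.44. The ratio is 0.99, so almost nothing is gained.
- The two SDs exchanged, r = 0.6 (in units of the smaller SD): the change variance is still 1.45 and the ANCOVA variance is 1 × 0.64 = 0.64. The ratio is 0.44, a larger gain than the 0.80 that equal SDs would give.
- k = 1.5, r = 0.8: the slope is 1.2, so the change score corrects too little. The shift is +0.2D, in the same direction as the imbalance.

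**The case against.** The strongest reply is that nothing planned here is invalid. Allocation is 1:1 and random, so the t test and the Wilcoxon test on changes keep their type I error, and the mean change comparison is unbiased on average. This stands. A reader might infer that the analysis is biased by regression to the mean. The documents do not support that: the distortion exists only conditionally on an imbalance that happens to occur.

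The reply also limits the size. A reader might take the first three rows of the table to mean that 15 to 35% of the sample is wasted on all these outcomes. That needs r between 0.3 and 0.7 and equal SDs, none of which the article gives, and four cycles of chemotherapy may well change the spread. It is likewise not general that a change score over-corrects whenever r is below 1, since what counts is rk. Nor does the formula measure the efficiency of a rank test. For skewed laboratory values a rank test can match or beat ANCOVA on untransformed data, and the simulation used normal data only.

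A reader might add that Wilcoxon results cannot be pooled over the planned multiple imputations. That is too strong. A rank-based estimate with its standard error can be combined, but this takes a further prespecified step.

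Finally, the stakes are bounded. The trial is sized on hair-loss grade, the section names Fisher's exact test on grade as the primary efficacy analysis, and FACT-B and the blood indicators are secondary.

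The reply does not show that baseline adjustment is provided elsewhere in the article, or that leaving it out has an advantage.

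**Conclusion.** The point holds as one of efficiency and of robustness to chance imbalance, and it should be acted on. It does not invalidate the plan. The article states unadjusted change comparisons outright for outcomes whose baselines it collects, and its only adjusted model cannot serve them.

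For hair diameter, the ANCOVA variance relative to the t test on change is 0.65 to 0.95 for r from 0.3 to 0.9, assuming equal SDs. The gain is clear at low to moderate correlation and small near 0.9. With unequal SDs it can be larger or close to nil, but in large samples it is not negative. For FACT-B and the blood indicators the direction of the argument is the same, but no size can be given from these formulas.

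**What to change.** Amend the Statistical analysis section as follows.

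- **Hair diameter before cycle 5:** ANCOVA with treatment and the baseline value as prespecified covariate. Report the adjusted mean difference with its 95% CI.
- **FACT-B and blood indicators at their planned visits:** the same model, or a rank-based ANCOVA if non-normality is the worry. Keep the Wilcoxon test on changes as a sensitivity analysis.
- **Baseline covariate:** include it whatever the observed baseline difference, and not through the data-driven rule given for the logistic model.

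An adjusted coefficient and its standard error also combine directly by Rubin's rules, which suits the multiple imputation already planned.

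The cost is a change of analysis wording. No visit, measurement or patient is added, and Fisher's exact test on hair-loss grade stays as it is. Further covariates such as centre or regimen, and transformations of laboratory values, can be settled in the analysis plan and are not part of this point.
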